#### Recruitment

Family participants will largely be identified through the Volunteer Family Connect usual service referral networks, which include child and family health nurses, general practitioners, or family support workers. The Volunteer Family Connect program is advertised within the community, and parents are welcome to self-refer to the program. If eligible for the program, families will be invited to speak to a member of the research team and, if interested, informed consent for the research will be secured. The family will then be randomly allocated by the research manager using computer-generated random numbers to receive either the volunteer home visiting program in addition to usual care services (Intervention group = Volunteer Family Connect + usual care services) or the usual care services only (Control group = usual care services).

The procedure used to recruit and allocate families is summarized in Figure 2.

An invitation will be extended to all volunteers currently involved with the 7 participating sites to participate in the research. The matched community comparison sample will be recruited via one of the following two strategies: (1) volunteers will be asked to pass on an invitation to participate in the research to nonvolunteering acquaintances in their local networks and (2) the research will be advertised through Facebook, targeting the local areas in which the Volunteer Family Connect program is being trialed.

#### Sample Size

We aim to recruit 300 families to the study, 150 to the intervention group (Volunteer Family Connect + usual services) and 150 families to the control group (usual services). Recruitment of 150 families per group has been undertaken based on what is feasible given current caseloads in the participating sites and also so that, allowing for attrition, data analysis can be conducted with a final sample size of 100 families per group. A sample size of 100 families per group has power of .80 at the 95% level to detect effect sizes (ESs) of .5 or larger for the PSCS Satisfaction subscale (significant differences detected with minimum n=16 per group) and the Client Enablement Index (significant differences detected with minimum n=7 per group) based on pilot study findings and a previous trial of nurse home visiting conducted by one of the chief investigators on this study [34].

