**Secondary Outcomes**									
	**Parent**								
		Parent physical and mental health	✓	✓	✓	✓	✓	✓	SF-12^a^ [40].
		General parent well-being	✓	✓	✓	✓	✓	✓	The Outcome Rating Scale [41].
		Parent empowerment	✓	✓	✓	✓	✓	✓	Modified Patient Enablement Instrument [42].
		Child-parent relationship	✓	✓	✓	✓	✓	✓	Parental questionnaire (questions from the Canadian National Survey of Parents of Young Children) [43].

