### Data Analysis

#### Quantitative Analysis

Primary and secondary outcomes will be extracted and analyses conducted using SPSS Version 25.0. Analysis will be completed both on an intention-to-treat and a per-protocol basis. Families will be considered to have received the scheduled dose if they receive visits from the volunteer for at least 3 months with no gap between visits of more than 2 weeks. Volunteer outcomes will be analyzed using cross-sectional comparative analysis. Participant demographic data will be analyzed using basic descriptive statistics. Prior to the analysis of outcome measures, data will be assessed for outliers and normality. Scale variables will be analyzed using independent *t* test or analysis of variance or their nonparametric counterparts (eg, Mann–Whitney U test) if appropriate. Mixed modeling will be completed on the primary and secondary family outcomes to assess the effect of the intervention over time while adjusting for possible confounders. Categorical variables will be analyzed using odd ratios or chi-square analysis. For all analyses, two-tailed tests will be undertaken: findings with α<0.05 will be determined to be statistically significant. ESs will be calculated for all trends (α<0.1) and statistically significant findings; (ES≈0.5 [Cohen *d*]) will be considered clinically meaningful. Overall, the program will be considered to have been effective if at least one of the primary outcomes is positive and the other is neutral.

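### The stated power of .80 does not match the design: 100 families per group give about 94% at d = 0.5, the quoted minimum sample sizes cannot refer to d = 0.5, and one of the two primary outcomes is not covered

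*Protocol article*

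**What the plan says.** The Sample Size section of the protocol article plans to recruit 150 families per group so that, after attrition, "data analysis can be conducted with a final sample size of 100 families per group". That number, it says, "has power of .80 at the 95% level to detect effect sizes (ESs) of .5 or larger for the PSCS Satisfaction subscale", and likewise for the Client Enablement Index. A minimum sample size is attached to each measure in brackets: "significant differences detected with minimum n=16 per group" for the subscale and "significant differences detected with minimum n=7 per group" for the index. The basis given is the pilot study and an earlier trial of nurse home visiting; no effect size or standard deviation from either is shown.

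The Quantitative Analysis section fixes the test: "For all analyses, two-tailed tests will be undertaken: findings with α<0.05 will be determined to be statistically significant". Scale variables go to an independent t test, analysis of variance or a nonparametric counterpart. A Cohen d of about 0.5 is the benchmark for clinical meaning.

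Table 1 lists two primary outcomes: community connectedness (Community Connectedness Scale and Social Provisions Scale) and parenting competence (Parenting Sense of Competence Scale, PSCS). Enablement appears there once, as the Modified Patient Enablement Instrument under parent empowerment, a secondary outcome. The name Client Enablement Index does not appear in the table.

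**The concern.** A power statement lets a reader judge what a null result means. Here three sets of figures stand in one sentence: 100 per group with power .80 at 0.5, a minimum of 16, and a minimum of 7. They do not come from one calculation at one effect size, so a reader cannot tell what effect the design was built to detect.

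The choice of outcomes also matters. Under the article's success rule the program counts as effective when one primary outcome favours it and the other shows no difference. Community connectedness can therefore decide the trial, or supply the neutral half of a success, yet the power statement does not mention it. It covers instead one subscale of the other primary instrument and a measure that is not listed as primary.

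**Working it through.** **Inputs.** 100 analysed families per group, power .80 and effect size 0.5 (Sample Size); two-sided alpha 0.05, independent t test and Cohen d (Quantitative Analysis). Equal groups are assumed, as the section's 100 per group implies.

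**Step 1: the stated figure.** Normal approximation: power = Φ(d·√(n/2) − 1.960) = Φ(0.5 × 7.071 − 1.960) = Φ(1.576) = 0.942. The noncentral t distribution gives 0.940. The article states .80, which is 14 points lower.

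**Step 2: what does match 80% power.**
- Sample size at d = 0.5: n = 2(1.960 + 0.842)²/0.5² = 2 × 7.849/0.25 = 62.8, so 63 per group; 64 with the t distribution.
- Detectable effect at n = 100: d = 2.802 × √(2/100) = 0.396; 0.398 with the t distribution, so 0.40.

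**Step 3: can another reading return .80?** Power at d = 0.5 (t distribution):

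| Variant | Power |
|---|---|
| One-sided 5% | 0.97 |
| Two-sided alpha 0.025 / 0.01 / 0.005 | 0.90 / 0.82 / 0.76 |
| Mann–Whitney, efficiency 0.955 / 0.864 | 0.93 / 0.90 |
| 200 families split 2:1 / 2.5:1 / 3:1 | 0.91 / 0.89 / 0.86 |
| 100 families in total (50 per group) | 0.70 |

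None falls within 2 points of 0.80. A design effect of about 1.6 would return it, but the article states none.

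**Step 4: the minimums of 16 and 7.** Three quantities, with the t distribution: power at d = 0.5; the d needed for 80% power (normal approximation 2.802 × √(2/n) in brackets); and the observed d that just reaches significance, t(0.975, 2n − 2) × √(2/n).

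| n per group | Power at d = 0.5 | d for 80% power | Just-significant d |
|---|---|---|---|
| 16 | 0.28 | 1.02 (0.99) | 2.042 × 0.354 = 0.72 |
| 7 | 0.14 | 1.63 (1.50) | 2.179 × 0.535 = 1.16 |

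On neither reading does 16 or 7 correspond to d = 0.5.

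**Step 5: outcomes covered.**

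| Measure | Status in Table 1 | Named in the power statement |
|---|---|---|
| PSCS | Primary | One subscale (Satisfaction) only |
| Community Connectedness Scale, Social Provisions Scale | Primary | No |
| Client Enablement Index | Not listed by this name; the only enablement instrument is secondary | Yes |

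**The case against.** The strongest reply is that nothing in the design suffers. The sentence speaks of effects of 0.5 or larger, so .80 is true as a lower bound, and the article says that recruitment was also set by what caseloads allow. This stands. A reader who sees a power figure that fails to reproduce might infer that the trial is too small; the calculation shows the opposite for d = 0.5.

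A reader might also infer that 16 and 7 flatly contradict the effect size of 0.5. The document does not support that. It does not define the minimums and ties the sentence to earlier studies whose results are not shown. Larger effects in those studies would fit the wording. The d values of about 1.0 and 1.6 rest on assuming 80% power and a two-sample t test; they are not the authors' figures. What remains is that the minimums say nothing about d = 0.5 and their source effects are missing.

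A third tempting reading is that the trial has no power for community connectedness. That does not follow either: power for a standardised effect at a given sample size does not depend on the scale. The Outcomes section adds that, where possible, tools were chosen that had shown group differences with at least 100 per group, although it concedes that many outcomes were new to home visiting research. The gap is that the statement leaves this primary outcome out.

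Finally, the section never calls its calculation a primary-outcome claim, and equating the Client Enablement Index with the secondary instrument is an inference. Under either name, though, it is not a listed primary outcome.

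**Conclusion.** The point holds as an error of statement, not of design. With 100 analysed families per group, a two-sided 5% two-sample t test and equal groups, power at d = 0.5 is 94%, not 80%. The chance of missing a true effect of that size is about 6% (1 − 0.94), against the 20% that the article implies, so a null result would count more strongly against d = 0.5 than a reader of the article would think.

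The minimums of 16 and 7 per group cannot refer to d = 0.5 and are uninterpretable without their source effect sizes. The statement should cover both primary outcomes and does not.

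The 94% assumes equal groups and independent families. The Allocation section permits proportional randomization when volunteers are short, with an example of five to two. If all 200 analysed families were split between 2:1 and 3:1, power would be about 91% to 86%, still above the stated figure. The calculation covers the simple two-group comparison, not the planned mixed models.

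**What to change.** Rewrite the power statement in the Sample Size section:

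- State that 100 analysed families per group give 80% power for d = 0.40 and about 94% for d = 0.5, with a two-sided 5% test and equal groups; and about 86% to 91% for d = 0.5 if 200 families end up split between 3:1 and 2:1 under proportional allocation.
- Apply the statement by name to both primary outcomes, parenting competence and community connectedness.
- Label the enablement figure as secondary, and use the same instrument name as in Table 1 if it is the same measure.
- Delete the minimums of 16 and 7, or report the effect sizes from the source studies that produced them and say what minimum means. The authors must supply those values; the back-calculated ones above should not be inserted in their place.

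If an allowance for clustering lay behind the .80, the authors should state it instead. The cost is a few sentences of text, with no change to recruitment, data collection or analysis.

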**Figure 2 figure2:**
[figure not shown]
Participant flow diagram.

The families will participate in data collection for a period of 15 months. Strategies have been put in place to support and encourage the retention of participants, including asking all participating parents to provide the name and phone number of a relative or friend who can be contacted by the researchers if we struggle to reach them; providing families with the contact details of the research team and asking them to advise us if their contact details change; providing each family with an Aus $20 gift voucher for a popular grocery store chain at each data collection point and sending thank you notes; and employing project offices who have strengths in the building of rapport with families. The decision to employ these strategies was primarily based on the positive experiences of the research team in the previous research projects [34,35].

A total of 80 volunteers and 80 comparison group members will be recruited to the study, reflecting current volunteer numbers.

#### Participant Timeline

Data collection spans a 15-month period so that there is at least one data collection point post family exit from the Volunteer Family Connect program (families receive the program for 3-12 months depending on their support needs). Volunteer outcomes will be measured over a 12-month period at 6-month intervals.

### Intervention

#### Development

The Volunteer Family Connect program was developed in conjunction with 3 leading not-for-profit organizations, all involved in coordinating volunteer home visiting programs in the eastern states of Australia: The Benevolent Society; Good Beginnings Australia (later subsumed into Save the Children Australia); and Karitane. An executive member from each partner organization along with the research leaders met every 6 weeks for approximately 5 years. Collaboratively, a “best practice” model of volunteer home visiting was developed based on a shared theory of change, the strengths of the existing programs, practice wisdom, and existing research evidence. The program was manualized, and practice tools were created such as fidelity checklists, family progress tools, and volunteer training schedules. The Volunteer Family Connect program is currently being implemented with fidelity in 7 trial sites across 4 states (New South Wales, Queensland, Tasmania, and Victoria) including city, suburban, and rural settings.

Preparation for the trial has also involved extensive and ongoing consultation and support for program coordinators and provision of training across all levels of the partner organizations (including volunteers) to increase the understanding of, and support for, the conduct of an RCT.

#### Pilot Study

Early preparatory work included a pilot and feasibility study. The methods and results of this small study comparing Volunteer Family Connect families with supported playgroup parents over a 6-month period have been reported elsewhere [36]. Family outcome measurement tools were piloted for face validity and ease of use, and the project survey instrument was refined in line with parent feedback and researcher experience of administration. The range of “usual care” programs and services (ie, programs and services available to all members of the community) were identified, and the processes for family recruitment to the trial and randomization were established and tested.

#### Delivery in the Trial

The families assigned to the intervention group will receive the Volunteer Family Connect program delivered by a volunteer associated with one of the partner organizations in the 7 trial sites. The Volunteer Family Connect program comprises the core components described below.

Program Coordinators: Each site has an employed program coordinator with tertiary qualifications in social work or a related field. The program coordinators are responsible for recruiting and training the volunteers, establishing referral networks, matching volunteers with families, providing regular supervision to volunteers, conducting intake and progress interviews with families, and referring families to other services within the community.Trained volunteers: All community volunteers participate in a minimum of 30 hours of training before being matched with a family and must participate in two additional capacity-building sessions each year. Examples of core training modules include “a strengths-based approach to working with families,” “reflection on personal values and attitudes,” “boundaries and self-care,” “child development,” and “community resources.” The topics for ongoing capacity-building sessions are decided by the program coordinator depending on family needs at the time. For example, if there are high numbers of families who have infants, topics like “breastfeeding” or “sleeping and settling” may be chosen. All volunteers undergo a background check.Matching: Program coordinators match families with a volunteer, guided by the needs of the family but limited by the pool of volunteers available.Home visits: Volunteers visit the family for approximately 2 hours every week. What happens during visits will depend on the needs of the family. Volunteers are encouraged to support families to connect with other services and facilities within the community (eg, attend local playgroups, visit the child and family health center, go to the park, etc) and link them with information as needed. Volunteers are also expected to model positive interactions with the children and encourage the parents in their personal and family goals. Volunteers do not do cooking or housework tasks unless it is with the parent as part of helping them to learn how to do these tasks, and they do not provide child-minding or child care such as changing nappies or bathing children. Volunteers complete checklists following each home visit, detailing the activities and topics of discussion with the family and whether information was provided to the family or the family linked with another service in the community. The collated data are used as a measure of program fidelity and provide ongoing quality feedback to the service partner organizations.Exit interviews: The duration of the service will be a minimum of 3 months and a maximum of 12 months. When the family, volunteer, and program coordinator agree that the family has met their goals, the family is exited from the program and referred to other services by the program coordinator as appropriate.

#### Control Group, Services as Usual

Neither intervention nor control group families are limited in the extent to which they are able to access other services within the community. It is anticipated that most families will access a range of early childhood health and education services. Family use of other services will be documented in the research, based on parent self-report, and explored as a variable in analysis.

**Table 1 table1:** Outcome measures.

Outcomes and Construct Measured			Data Collection Schedule						Instrument
			Enrollment (Baseline)	Months					
				3	6	9	12	15	
**Primary Outcomes**									
	Community connectedness		✓	✓	✓	✓	✓	✓	Community Connectedness Scale [37]; Social Provisions Scale [38].
	Parenting competence		✓	✓	✓	✓	✓	✓	Parenting Sense of Competence Scale [39].
**Secondary Outcomes**									
	**Parent**								
		Parent physical and mental health	✓	✓	✓	✓	✓	✓	SF-12^a^ [40].
		General parent well-being	✓	✓	✓	✓	✓	✓	The Outcome Rating Scale [41].
		Parent empowerment	✓	✓	✓	✓	✓	✓	Modified Patient Enablement Instrument [42].
		Child-parent relationship	✓	✓	✓	✓	✓	✓	Parental questionnaire (questions from the Canadian National Survey of Parents of Young Children) [43].
	**Child**								
		Immunization	✓	✓	✓	✓	✓	✓	Child Personal Health Record.
		Nutrition or breastfeeding	✓	✓	✓	✓	✓	✓	Parental questionnaire-Breastfeeding questions from the New South Wales Child Health Survey (CHS; CHS items CBF^b^1, CBF2, and CBF13) [44].
		Accidental injury	✓	✓	✓	✓	✓	✓	Parental questionnaire: “In the last 3 months, did your children get injured at home? If yes, did the injury require medical attention (eg, your child needed to go to a hospital emergency room or general physician for medical attention)?”
	**Family**								
		Sustainability of family routines	✓	✓	✓	✓	✓	✓	Ecocultural Family Interview [45].
	**Service use**								
		Satisfaction with the VFC^c^ program and other services being accessed	✓	✓	✓	✓	✓	✓	Checklist of local community services. Modified Patient Satisfaction Questionnaire Short Form [46]. Rating of Expectations identified at program entry on a 10-point Likert Scale *(intervention only).* Semistructured interview at program exit to reflect on experience of program participation *(intervention only)*.
	**Volunteer**								
		Volunteer mental and physical health	✓		✓		✓		SF-12 [40].
		Guidance, reassurance of worth, social integration, nurturance, reliable alliances, and attachment	✓		✓		✓		Social Provisions Scale [38].
		Social connectedness and knowledge of community resources	✓		✓		✓		Community Connectedness Scale [37].
		Confidence or belief in meaningfulness of volunteer participation	✓		✓		✓		Community Service Self-Efficacy Scale [47,48].
		Motivational drives of volunteers	✓		✓		✓		Volunteer Motivation Inventory [49].
	**Process**								
		Volunteer activities or Experience of program participation		✓^d^	✓^d^	✓^d^	✓^d^	✓^d^	Visit record sheet checklist is completed at every visit. Volunteer visits weekly for a minimum of 3 mo and a maximum of 12 mo. Volunteer completes a checklist of topics and activities covered during the visit and qualitative questions, including volunteer perception of the impact of the program on the family.

^a^SF-12: 12-Item Short Form Health Survey.

^b^CBF: child breastfeeding.

^c^VFC: Volunteer Family Connect.

^d^Collected weekly for the duration of the intervention.

### Outcomes

In keeping with the processes of a pragmatic randomized trial [37], primary and secondary outcomes were chosen in collaboration with the partner organizations and in consultation with volunteers and families, based on their perceptions of the expected benefits of volunteer home visiting and the importance of the outcome to the families and their volunteers. Discussions on appropriate outcomes were conducted in monthly steering committee meetings with senior representatives from all partner organizations, in focus groups with volunteers held in every participating site, and in focus groups with families conducted within the Sydney-based sites. Wherever possible, tools previously demonstrated to have power to show significant differences between the intervention and comparison groups with a minimum of 100 participants per group were selected; however, many of the expected outcomes have not previously been measured in home visiting studies. With the exception of the home visiting program satisfaction scale (intervention group only), measures are identical for both family intervention and comparison groups. Measures are identical for the volunteer group and the matched community comparison group. In addition, program process data will be collected. The measures are presented in Table 1.

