### Secondary Research Questions

Do differences exist in the patterns of parent health, well-being, and empowerment and the sustainability of family routines over time between those who receive the Volunteer Family Connect program and those in the services as usual control group?Does volunteer home visiting lead to differing outcomes for children aged 0-5 years in intervention families compared with those in control group families on measures of immunization, breastfeeding duration, nutrition, and accidental injury?Do different patterns of outcomes for intervention families depend on the location (ie, availability and accessibility of health, welfare, and early childhood services in the local area) and the duration of the program (ranging from 3 to 12 months)?Does volunteering on the Volunteer Family Connect program lead to differing outcomes on measures of well-being, health, community connectedness, and self-efficacy for volunteers over time compared with a matched community comparison group?

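### The Volunteer Motivation Inventory goes unchanged to a comparison group sought partly as non-volunteers, self-efficacy is compared cross-sectionally in volunteers already serving, and the comparator is defined differently by recruitment route

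*Protocol article*

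**What the plan says.** Outcomes fixes which instruments each volunteer-study group receives: "Measures are identical for the volunteer group and the matched community comparison group". The sentence just before it deals with the families and does make an exemption: "With the exception of the home visiting program satisfaction scale (intervention group only), measures are identical for both family intervention and comparison groups". No such exemption is made for the volunteer study.

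Table 1 lists five volunteer constructs, each at baseline, 6 and 12 months. Three use general instruments (SF-12, Social Provisions Scale, Community Connectedness Scale). Two are labelled by volunteering: "Confidence or belief in meaningfulness of volunteer participation", measured by the Community Service Self-Efficacy Scale, and "Motivational drives of volunteers", measured by the Volunteer Motivation Inventory.

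The fourth secondary research question asks about "well-being, health, community connectedness, and self-efficacy for volunteers over time compared with a matched community comparison group". It does not name motivation.

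Under Recruitment, comparators come by two routes. In the first, "volunteers will be asked to pass on an invitation to participate in the research to nonvolunteering acquaintances in their local networks". The second is Facebook advertising in the trial areas, with no condition about volunteering. Under Eligibility Criteria, the volunteer group consists of people already in the program, and comparators are matched on age, gender, education, employment and location. Data Analysis plans a cross-sectional comparison of volunteer outcomes; the mixed models described there are for family outcomes. Sample Size gives 80 volunteers and 80 comparators.

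**The concern.** Three things do not fit together.

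First, an inventory of why volunteers volunteer is given to people at least some of whom are recruited because they do not. A difference between the groups on it says something about who volunteers, not about what volunteering does. The research question does not ask for this contrast, but the plan as written leads to it: the inventory is a listed volunteer outcome, both groups complete it, and volunteer outcomes are compared between groups.

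Second, self-efficacy is a stated between-group outcome. People who chose to volunteer may well differ on it from people who did not, for reasons that precede the program. Matching does not cover volunteering history or disposition. A cross-sectional comparison cannot separate such a gap from an effect, although the research question asks about outcomes over time.

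Third, the comparator is a non-volunteer by one route and undefined by the other, so the meaning of every volunteer contrast depends on the mix of routes.

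At stake is a difference that reflects who signs up being reported as a benefit to volunteers, in a study presented as the first to examine outcomes for both families and volunteers.

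**Working it through.** The volunteer sample has no power statement, so there is no figure of the plan's own to reproduce. The first and third parts are a matter of reading; the second can be illustrated.

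**1. Motivation inventory.**
- Outcomes: same measures in both groups, no exemption.
- Table 1: the inventory is a volunteer outcome, and its label presupposes a volunteer.
- Data Analysis: volunteer outcomes are compared between groups.
- Recruitment: one route asks for people who do not volunteer.

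Together these produce a motivation contrast that answers no stated question. This concerns 1 of 5 volunteer instruments.

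**2. Self-efficacy under a cross-sectional test.** This concerns 1 of the 4 constructs named in the volunteer question.

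Inputs from the protocol: n = 80 per group (Sample Size); two-sided 5% (Data Analysis). Assumed, not from the protocol: a constant gap of d standard deviations that exists for reasons other than an effect of volunteering, and no change caused by volunteering during follow-up.

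Standard error of the difference in SD units: √(2/80) = 0.158.

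P(significant) = Φ(d/0.158 − 1.96) + Φ(−d/0.158 − 1.96)

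| Assumed gap d | P(significant) |
|---|---|
| 0 | 0.05 |
| 0.2 | 0.24 |
| 0.3 | 0.48 |
| 0.44 | 0.80 |
| 0.5 | 0.89 |
| 0.8 | above 0.99 |

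A simulation (2000 runs, assumed baseline to follow-up correlation r = 0.6) gave 0.49, 0.88 and above 0.99 for the cross-sectional test at d = 0.3, 0.5 and 0.8. Testing change from baseline instead gave 0.063, 0.051 and 0.050.

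The form of baseline adjustment matters because the groups are not randomized. With follow-up = r × (baseline − d × group) + d × group + error, the group coefficient after entering baseline as a covariate is (1 − r) × d. At r = 0.6 and d = 0.5 that leaves 0.4 × 0.5 = 0.2 SD. Under a constant gap, the change score removes the gap and the covariate model removes only part of it.

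**3. Comparator definition.** If a share v of comparators volunteers elsewhere with the same benefit, the expected contrast is (1 − v) × the true effect. The protocol gives nothing from which to judge v. An assumed 10% to 30% gives a shrinkage of 10% to 30%, which only restates the assumption.

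**The case against.** The strongest reply is that the item wording of both scales is absent. A reader might infer from the construct labels that non-volunteers cannot answer the self-efficacy scale and that the groups therefore differ on it by definition. The protocol does not support that: the scale's title refers to community service in general, and confidence or belief about such service can be asked of someone not currently serving. This part of the reply stands, and self-efficacy should not be called invalid.

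A second reply is that no motivation contrast is named in the research question. That is true, but the unqualified statement on identical measures and the cross-sectional plan for volunteer outcomes still lead to one.

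A third is that self-selection affects any non-randomized comparison, and that the protocol openly explains why volunteers cannot be randomized. This also stands. The probabilities above illustrate an assumed standing gap; they are not evidence about volunteer-worded items, and the same reasoning would apply to a standing gap on the general scales.

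A fourth is that the Facebook route is merely silent, that screening detail may sit in a fuller protocol, and that community members with other voluntary activities can be a fair comparator for volunteering on this particular program. Either definition can be defended. What is not satisfactory is that the article states the condition for one route and not the other.

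Finally, removing comparators from the self-efficacy analysis would discard the only control for time trends and repeated measurement. That is a good reason to keep the comparison.

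**Conclusion.** The point holds in a limited form. A between-group comparison on the Volunteer Motivation Inventory has no clear meaning as an effect of volunteering. The self-efficacy comparison is interpretable only with caution: it is confounded with the choice to volunteer, and the cross-sectional plan would turn a standing gap into an apparent effect (about 48% of the time at an assumed 0.3 SD, 89% at 0.5 SD, with 80 per group). These probabilities rest wholly on the assumed gaps and show how sensitive the plan is, not how large the bias will be. The comparator is defined unevenly across the two routes, and the resulting dilution, if any, cannot be sized from the protocol.

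A reader might go further and infer that the volunteer findings as a whole fail. The document does not support this. The SF-12, Social Provisions Scale and Community Connectedness Scale do not share the wording problem, and the Abstract's list of volunteer outcomes (health, well-being, community connectedness) includes neither self-efficacy nor motivation. This is a minor point in a non-randomized secondary sub-study.

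**What to change.** - **Outcomes.** Qualify the statement on identical measures so that the Volunteer Motivation Inventory is completed and reported within volunteers only, as description at baseline, 6 and 12 months.
- **Data Analysis.** Keep the self-efficacy comparison but adjust it for the baseline value already collected. Name the form: change from baseline (or the equivalent group-by-time term) fits a constant gap, with the covariate model as a sensitivity analysis. State that baseline in current volunteers is already after exposure, so the result concerns continued volunteering, and confirm that the scale is comparable across the two groups.
- **Recruitment.** Apply one condition, not currently volunteering, to both routes, or record current volunteering and repeat the comparison without comparators who volunteer.

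The cost is some rewording, a shorter comparator survey, one screening question, one fewer between-group volunteer measure and possibly a few Facebook recruits lost. The article describes data collection as under way. For comparators already enrolled, the inventory can still be left out of the group comparison, and current volunteering can be asked at a remaining survey.
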